### 9.2 Sample Size

We base our sample size justification on prior data from our RESTORE and PRIME pilot studies, two-tailed tests conducted at the  $\alpha=0.05$  level, a conservative attrition rate of 10% between baseline and follow-up assessments, practical consideration of a class size of 10 participants for group exercise, computational techniques that match our study design and proposed analytical approach as much as possible within the constraints of already published methodologies and commercially available sample size and power software (PASS 2002®, Number Cruncher Statistical Systems, Inc., Kayesville, Utah), and ability to detect differences that correspond to published meaningful change criteria(57) or moderate Cohen's effect sizes of  $d=0.5$ .(58)

The numbers needed to enroll in order to detect statistical significance of intervention effect when delivered by an exercise leader (Aim 1), are presented in **Table 1**. We take into account the clustering of participants by facility by assuming an intracluster correlation of 0.1 and a resulting design effect of 1.90 to appropriately inflate the sample size accordingly.(59) In

summary, a total of 280 participants with 140 in each arm will allow us to detect statistical significance in intervention effects in all main outcomes with at least 80% statistical power.

**Table 1. Number needed to enroll for detecting effects of intervention incorporating clustered design (x1.90), attrition (10%), and rounded up to class size of 10.**

| Outcome                    | Prior Information                |                                 |                                         | Estimated Sample Size                                   |                                 |
|----------------------------|----------------------------------|---------------------------------|-----------------------------------------|---------------------------------------------------------|---------------------------------|
|                            | Baseline Standard Deviation (SD) | SD in Baseline-Follow up Change | Meaningful Difference Targeted (Source) | Completers Needed Per Arm assuming No Clustering | Number Needed to Enroll Per Arm |
| LLFDI Overall Function     | 6.15                             | 4.86                            | 3.08 ( $d=0.5$ )                        | 41                                                      | 90                              |
| LLFDI Disability Frequency | 6.35                             | 4.76                            | 3.18 ( $d=0.5$ )                        | 37                                                      | 80                              |
| Gait Speed (m/s)           | 0.13                             | 0.20                            | 0.10                       | 64                                                      | 140                             |
| 6MWD (m)                   | 62.0                             | 42.8                            | 50                         | 13                                                      | 30                              |

Our sustainability Aim 2 depends on whether we are able to train a staff activity person ready to lead a class safely and per protocol. Further, we do not have a priori data in sufficient detail that allows us to reliably estimate the likelihood of suitably training a staff activity person in each of the main type of facility. Thus Aim 2 is exploratory in nature and we will also focus on barriers to suitably training a staff activity person. We anticipate that we will enroll approximately 120 participants into Aim 2. The power available to detect a statistically significant difference in gains attributable to *On the Move* when delivered by exercise leaders and staff activity personnel (sustainability hypothesis – Aim 2) are in **Table 4**. Power is  $\geq 90\%$  for all outcomes except for gait speed when comparing *On the Move* to Standard when delivered by facility staff in which case power is 78%.

1029 **Table 4. Number needed to enroll for establishing sustainability of *On the Move*, incorporating clustered design**  
 1030 **(x0.90), attrition (10%), and rounded up to class size of 10.**

| Outcome                    | Prior Information                |                                 |                                         | Estimated Sample Size                                      |                                 | New Aim 2 Statistical Power with Anticipated N=140+140+60+60                |                                                                                       |
|----------------------------|----------------------------------|---------------------------------|-----------------------------------------|------------------------------------------------------------|---------------------------------|-----------------------------------------------------------------------------|---------------------------------------------------------------------------------------|
|                            | Baseline Standard Deviation (SD) | SD in Baseline-Follow up Change | Meaningful Difference Targeted (Source) | Completers
Needed Per Arm assuming No Clustering | Number Needed to Enroll Per Arm | Facility Staff as Good as Exercise Leader in Delivering OTM?
N=140 vs 60 | OTM More Effective than Standard Even when Delivered by Facility Staff?
N=60 vs 60 |
| LLFDI Overall Function     | 6.15                             | 4.86                            | 3.08 ( $d=0.5$ )                        | 66                                                         | 70                              | 98%                                                                         | 93%                                                                                   |
| LLFDI Disability Frequency | 6.35                             | 4.76                            | 3.18 ( $d=0.5$ )                        | 60                                                         | 60                              | 99%                                                                         | 95%                                                                                   |
| Gait Speed (m/s)           | 0.13                             | 0.20                            | 0.10                       | 105                                                        | 110                             | 90%                                                                         | 78%                                                                                   |
| 6MWD (m)                   | 62.0                             | 42.8                            | 50                         | 21                                                         | 30                              | >99%                                                                        | >99%                                                                                  |

1031  
 1032  
 1033

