## 9 STATISTICAL CONSIDERATIONS

### 9.1 General Design Issues

A randomized trial is needed to control for confounding factors that affect the outcome. There are no ethical issues regarding a randomized trial since both groups will be receiving an active exercise intervention delivered by trained personnel. We carefully considered the advantages and disadvantages of randomizing at the level of the facility and the resident. Given the amount of interaction that occurs between subjects within a facility, it is imperative that we conduct a cluster randomized trial, and randomize by facility to exercise programs. If we randomize at the resident, participants would discuss details of their intervention and cause cross-contamination between the intervention arms. Unlike a traditional trial in which participants are randomized as they are being recruited, a cluster randomized trial also affords the additional benefit of examining the facility characteristics such as type (independent living/senior high rise) and size, and ensuring a balance in those characteristics is achieved by design rather than chance. Once the facilities are randomized to exercise program, we will then randomize within facility for delivery mode (i.e. subjects will be randomized to either an exercise leader or staff activity person led exercise program). Randomization for delivery mode will occur after baseline testing. We will use a commercially available high quality pseudo-random deviate generator such as that available in SAS® (SAS Institute, Inc., Cary, North Carolina) known to be free of serial correlations(56) to randomize facilities to the two arms in a 1:1 ratio, stratified by facility type. In addition, the proposed design reaps the advantages of a paired comparison for the exploratory hypothesis (Aim 2) as both exercise leaders and staff activity personnel will be delivering On the Move in the same set of facilities, where feasible to train a staff person ready to lead the class safely and per protocol.

The main outcomes are self-reported function and disability (Late Life Function and Disability Index/LLFDI) and walking ability (6-minute walk test/6MWT and gait speed). We will also examine satisfaction, attendance rates and adverse event (falls, soft tissue injuries, muscle soreness, etc) rates.

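### Table 4's power for staff-led On the Move versus staff-led Standard (60 vs 60) omits the between-facility design effect, so the printed 93%, 95% and 78% are too high

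*Supplement*

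**What the plan says.** All references are to protocol Version 2.0.

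- **Unit of randomisation (Section 9.1).** Because residents of one facility interact, "it is imperative that we conduct a cluster randomized trial, and randomize by facility to exercise programs". Only delivery mode (exercise leader or staff) is randomised within a facility. The benefit of pairing is claimed for leader against staff delivery of On the Move in the same facilities, where a staff person can be trained.
- **Aim 1 sizing (Section 9.2, Table 1).** On the Move is compared with Standard by "assuming an intracluster correlation of 0.1 and a resulting design effect of 1.90 to appropriately inflate the sample size accordingly". For gait speed this leads to 140 per arm for 80% power.
- **Aim 2 power (Section 9.2, Table 4).** The title gives the adjustments as ("x0.90), attrition (10%), and rounded up to class size of 10"). The columns headed "New Aim 2 Statistical Power with Anticipated N=140+140+60+60" cover two contrasts: leader versus staff delivery of On the Move (140 vs 60), and staff-led On the Move versus staff-led Standard (60 vs 60). The second shows 93%, 95%, 78% and >99% for LLFDI function, LLFDI disability frequency, gait speed and 6MWD.
- **Text before Table 4.** It claims at least 90% power throughout, the one exception being gait speed for On the Move compared "to Standard when delivered by facility staff in which case power is 78"%.

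**The concern.** Staff-led On the Move and staff-led Standard never share a facility. Apart from who leads the class, this is the same facility-randomised contrast as Aim 1, for which the plan inflates by 1.90. The two tables do not fit together. With the same gait-speed inputs (SD of change 0.20, difference 0.10 m/s), Table 1 needs 140 per arm for 80% power, while Table 4 reports 78% from 60 per arm.

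What is at stake is how Aim 2 will be read. Section 9.3.3 still treats significance of these contrasts as the formal hypothesis tests. A null gait-speed result under staff delivery would be taken as coming from a test with nearly 80% power, when its power may be near one half.

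**Working it through.** **Inputs (Section 9.2, Tables 1 and 4).** Tests are "two-tailed tests conducted at the" 0.05 level. Attrition is "a conservative attrition rate of 10% between baseline and follow-up assessments". Clustering for program comparisons is set by "assuming an intracluster correlation of 0.1 and a resulting design effect of 1.90", that is 1 + (10 − 1) × 0.1 = 1.90. Standardised differences use the SD of change:

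- LLFDI function: 3.08/4.86 = 0.634
- LLFDI disability frequency: 3.18/4.76 = 0.668
- Gait speed: 0.10/0.20 = 0.500
- 6MWD: 50/42.8 = 1.168

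**Formula.** Effective n per arm = 60 × (1 − attrition)/DE. Power = Φ(d × √(n/2) − 1.96).

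**Step 1: reproduce the printed column.** With the table's 0.90, n = 60 × 0.9/0.90 = 60, so attrition and the pairing factor cancel. For gait speed, 0.5 × √30 = 2.739 and Φ(0.779) = 78.2%.

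| Outcome | Printed | Normal, n = 60 | t test, n = 60 |
|---|---|---|---|
| LLFDI function | 93% | 93.5% | 93.1% |
| LLFDI disability frequency | 95% | 95.5% | 95.2% |
| Gait speed | 78% | 78.2% | 77.5% |
| 6MWD | >99% | >99.9% | >99.9% |

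Ignoring attrition and clustering altogether gives the same numbers. Either way, 1.90 was not applied. With 10% attrition and no clustering (54 per arm), gait-speed power would already fall to 73.8%.

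**Step 2: apply the plan's between-facility factor.** n = 54/1.90 = 28.4 per arm. For gait speed, 0.5 × √14.21 = 1.885 and Φ(−0.075) = 47.0%. The same step gives 66.6% for function, 71.2% for disability frequency and 99.3% for 6MWD. The t version gives 65.1%, 69.6%, 45.7% and 99.1% (function, disability frequency, gait speed, 6MWD).

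**Step 3: vary the design effect (assumptions).** Power by the normal formula with 54 completers per arm:

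| Setting | DE | Function | Disability | Gait speed |
|---|---|---|---|---|
| Classes of 10, staff data alone | 1.90 | 66.6% | 71.2% | 47.0% |
| Joint mixed model, staff classes in 6 facilities per arm | 1.54 | about 75% | about 80% | about 55% |
| About 5 staff-led participants per facility | 1.40 | 79.5% | 83.5% | 59.3% |
| About 3.5 per facility | 1.25 | 83.8% | 87.4% | 64.2% |

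The 1.54 comes from generalised least squares with ICC ρ = 0.1. In a facility with both class types, the two class means have variances ρ + (1 − ρ)/m and covariance ρ; a leader-only facility contributes its leader mean. I took 126 leader completers per arm over 14 or 17 facilities (28 or about 34 sites, halved) and 54 staff completers over 6.

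**Step 4: the 140 vs 60 column.** With 0.90, 126 vs 54 completers again become 140 vs 60. For gait speed, 0.5/√(1/140 + 1/60) = 3.240 and Φ(1.280) = 90.0%, as printed. If staff classes ran in only 6 of the 14 or 17 On the Move facilities (an assumption), the Step 3 model gives design effects of 1.08 and 1.12, and power of 84.1% and 82.6%.

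**The case against.** **Aim 2 is exploratory.** The plan says so, fixes no sample size for it, and stops enrolment when Aim 1 reaches 280. Nothing in the sizing of the trial depends on this column, and Table 1, which does size it, applies 1.90 and reproduces. That limits the consequence but does not make the printed figures right.

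**1.90 may be too severe here.** Ten is a class maximum (Section 3), and Section 4 says numbers per site will vary. Smaller staff classes mean a smaller design effect. Section 9.3.3 also fits one mixed model to all four program-by-delivery groups, so leader-class participants help estimate the facility effects. Both points stand, and they are why a range is needed.

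**Stronger readings that the documents do not support.** A reader might infer that true power is 47%, 67% and 71% or lower. A t test on 12 facilities (10 df) does give about 40%, 58% and 62% (gait speed, function, disability frequency), but it assumes full classes and a staff-only analysis, which is not the planned model. The departures considered above mostly raise power. A reader might also infer that the 140 vs 60 column is plainly wrong. That depends on how many facilities host a staff class, which the plan does not state, and Section 9.1 already limits the pairing to facilities where it is feasible.

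**Conclusion.** The 60 vs 60 column is wrong as printed. It reproduces only with an effective 60 independent participants per arm, although the comparison is between randomised facilities. On the plan's own ICC, class size and attrition, power is about 67% (LLFDI function), 71% (LLFDI disability frequency) and 47% (gait speed). With design effects of about 1.54 down to 1.25, it is about 75-84%, 80-87% and 55-64%. All these values are below the printed ones, and the claim of at least 90% power outside gait speed fails for both LLFDI outcomes throughout this range. 6MWD is essentially unchanged.

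The range rests on assumed participants and staff classes per facility. The 140 vs 60 column warrants only a note that 0.90 assumes a staff class in every On the Move facility. Aim 1 and its 280 participants are untouched.

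**What to change.** 1. Replace the last column of Table 4 with the design-effect-1.90 figures (67%, 71%, 47%, 99%), and state that x0.90 does not apply to it.
2. Beside it, show the range for smaller design effects, with the assumed participants per facility and any credit taken for leader-class data.
3. Correct the sentence in Section 9.2 that gives at least 90% power for everything except gait speed at 78%.
4. Describe the staff-led effectiveness contrast as exploratory estimation with confidence intervals, in Section 9.2 and in the Aim 2 part of Section 9.3.3.
5. Add a note to the 140 vs 60 column on the full-pairing assumption, with gait-speed power of about 82-84% if staff classes run in only about 6 of 14-17 On the Move facilities.

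The cost is one table and a few sentences, and a less favourable power statement for Aim 2. No participants or visits are added.

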### 9.3 Data Analyses

#### 9.3.1 Overview

All statistical analyses will be performed or overseen by [name] using SAS® version 9 (SAS Institute, Inc., Cary, North Carolina) and Salford Predictive Miner® (Salford Systems, Inc., San Diego, California) based on the **intention-to-treat** philosophy. We will begin by summarizing data by arm and time point as well as pre- to post-intervention change using appropriate descriptive statistics for continuous (mean, standard deviation, median, range) and categorical (frequencies, percentages) to elicit information about general data quality and their distributional characteristics. Next, we will perform the modeling and inferential analyses to address the main hypotheses. First, the baseline participant characteristics will be compared between the two arms (see Avoidance of Bias below). Although no significant differences are expected, any significant differences will be noted and accounted for as covariates in the main analyses. Second, main analyses to address Aims 1-3 will be performed as outlined below. If residuals reveal violations of linear models assumptions, we will Box-Cox transform(60) the response variables. The two-step protected test approach will be used to control the experimentwise type I error rate from multiple outcomes, and multiple imputation(61, 62) will be used to account for any missing data in the main analysis. Third, we will perform the exploratory analyses to address Aim 4, using a data mining philosophy. Finally, we will perform a set of exploratory analyses to potentially extend our findings and generate new hypotheses, as well as a set of sensitivity analyses to assess the robustness of our findings.

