### **1.2 Secondary Objectives**

**Aim 2: When feasible to be delivered by staff activity personnel, explore the effectiveness of *On the Move* compared to a standard program; and sustainability compared to delivery by exercise leaders (when feasible). Explore barriers to identifying and training staff activity personnel.** *On the Move delivered by staff activity personnel (when feasible) will produce gains in above outcomes that are greater than the standard program; and comparable to when delivered by an exercise leader.*

**Aim 3: Explore the acceptability and the risks of the *On the Move* and standard exercise programs delivered by (a) exercise leaders and (b) staff activity personnel (when feasible).** *On the Move will result in greater satisfaction and higher attendance rates than the standard program. Attendance rates and satisfaction will be similar for exercise leader and staff activity personnel led programs when feasible to recruit staff personnel. Adverse event (falls, soft tissue injuries, muscle soreness, etc.) rates during exercise will be similar between the two groups and the two facilitators when feasible to recruit staff personnel.*

**Aim 4: Explore potential baseline predictors of benefit and risks of participation in *On the Move* program to facilitate informed patient decision making.** *We will be able to identify combinations of baseline physical, psychosocial and demographic factors associated with each of the treatment response and adverse events outcomes.*

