#### 9.3.2 Main Analysis for Aims 1 and 3a

##### Aim1:

First, we will perform a multivariate Hotelling *t*-test to simultaneously compare the baseline to follow-up change in the three primary outcomes between the arms to protect the type I error rate from multiplicity. If significant, subsequent analyses will be performed without further multiplicity adjustment. If not, subsequent comparisons will be performed with a conservative Bonferroni correction at the  $\alpha=0.05/4=0.0125$  level. This protected test approach has been recommended in the statistical literature(63) and used in other exercise intervention trials with multiple outcomes.(64)

Second, we will fit a series of linear mixed models(65) using the SAS® MIXED procedure with baseline to follow-up change in each of the continuous outcomes (LLFDI function/disability, walking ability, other measures of mobility performance) as the dependent variable; intervention arm (standard/*On the Move*), as the fixed effect of primary interest; baseline value of outcome as an additional fixed effect covariate; and a facility random effect to account for greater similarity of participants from the same facility compared to different facilities and resulting non-independence of observations within facility (ie. clustering). We will construct appropriate means contrasts to estimate difference in gains in the two interventions when delivered by exercise leaders (Aim 1) whose statistical significance of the estimates will serve as formal tests of hypotheses. We will consider adding other baseline measures found to be significantly

different between the arms or deemed important as additional fixed effect covariates in the model to assess robustness of the findings. We note that waiting of participants randomized to staff activity personnel classes constitute a group of control participants, if smaller, without any intervention. Therefore, we will perform another sensitivity analysis employing a similar analytic strategy but with three intervention arms (*On the Move*/Standard/Wait List Control).

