#### Aim 3(a):

We will fit a series of generalized estimating equations (GEE) models using the SAS® GENMOD procedure with each of the dichotomous adverse events, adherence (21+ sessions or  $\geq 90\%$ ) and satisfaction outcomes as the dependent variable; a binomial distribution for the outcome and a logit canonical link function; intervention arm, as the effect of primary interest; baseline value of outcome and any other measures found to be different between arms or deemed important as additional fixed effects covariates; and an exchangeable working correlation structure to account for clustering due to facility. We will appropriately construct contrasts to test hypotheses of differential proportions with adverse events based on intervention when delivered by exercise leaders.

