#### 9.3.3 Aims 2, 3(b) and 4 exploratory Analyses

##### Aim 2:

We propose an analytic strategy with an exploratory philosophy for Aim 2 sustainability aim, because of the uncertainty surrounding our ability to recruit and train a staff activity person to lead a class safely and per protocol.

We will fit a series of linear mixed models using the SAS® MIXED procedure with baseline to follow-up change in each of the continuous outcomes (LLFDI function/disability, walking ability, other measures of mobility performance) as the dependent variable; intervention arm (standard/*On the Move*), delivery mode (by exercise leader/staff activity personnel) and their interaction as fixed effects of interest; baseline value of outcome and any other measures found to be different between arms or deemed important as additional fixed effects covariates; and a facility random effect to account for greater similarity of participants from the same facility compared to different facilities and resulting non-independence of observations within facility (ie. clustering). We will construct appropriate means contrasts to estimate difference in gains in the two interventions when delivered by staff exercise personnel (Aim 2 effectiveness hypothesis); and difference in gains attributable to *On the Move* intervention when delivered by exercise leaders and staff activity personnel (Aim 2 sustainability hypothesis). Statistical significance of the estimates will serve as formal tests hypotheses. We note that participants randomized to staff activity personnel had to wait 12 weeks since their baseline assessment and randomization to start the intervention, during which they may have changed; and that they underwent a second baseline assessment immediately prior to starting the exercise intervention. Therefore, we will repeat the above analysis using their second baseline assessment instead of the first one to assess the sensitivity of results.

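### Aims 2 and 3 are exploratory in the objectives but partly main or formally tested in the analysis section, and the plan's only multiplicity rule does not cover them or the additional mobility measures

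*Supplement*

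**What the plan says.** All references are to protocol Version 2.0 in the Supplement.

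**Status of the aims.**
- Section 1.2 opens Aim 2 with the verb explore, and opens Aim 3, covering both (a) and (b), with "Explore the acceptability and the risks of the" two programs. It still attaches directional hypotheses, for example "On the Move will result in greater satisfaction and higher attendance rates than the standard program".
- Sections 9.1 and 9.2 also call Aim 2 exploratory. The heading of 9.3.3 puts Aims 2, 3(b) and 4 under exploratory analyses.
- Section 9.3.1 states that "main analyses to address Aims 1-3 will be performed as outlined below" and then names only Aim 4 as the aim to be explored.
- Section 9.3.2 is headed as the main analysis for Aims 1 and 3a. Its Aim 3(a) block says: "We will appropriately construct contrasts to test hypotheses of differential proportions with adverse events based on intervention when delivered by exercise leaders".
- Section 9.3.3, having given Aim 2 an exploratory philosophy, adds: "Statistical significance of the estimates will serve as formal tests hypotheses".

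**Error control.**
- Section 9.3.1 says a two-step protected approach will control the experimentwise type I error across multiple outcomes.
- The rule itself appears once, under Aim 1 in 9.3.2. A Hotelling test compares the arms on three primary outcomes. If it is significant, "subsequent analyses will be performed without further multiplicity adjustment". If not, comparisons use a "Bonferroni correction at the $\alpha=0.05/4=0.0125$ level".
- The Aim 1 mixed models cover LLFDI, walking ability and the other mobility measures in one series, and significance of the resulting contrasts is the formal test.
- No alpha is given for Aims 2 or 3. The nearest statement is in section 9.2, which bases the sample size on "two-tailed tests conducted at the $\alpha=0.05$ level".

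**The concern.** The same result can be given two standings. An analyst holding a single p<0.05 on satisfaction, attendance or an adverse event in the exercise-leader classes could call it a main result under 9.3.1 and 9.3.2, or an exploratory one under 1.2. For Aim 2, the exploratory label sits beside a formal significance rule. That choice would be left open until the data are seen.

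The claim of experimentwise control is also broader than the rule behind it. A significant Hotelling test on three primary outcomes says that at least one of them differs between arms. It says nothing about gait efficacy, figure-of-8, challenging gait tasks, gait variability or SPPB. Once a real primary effect opens the gate, null outcomes among these have no protection.

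What is at stake is which secondary findings on acceptability, safety, sustainability and mobility may be presented as confirmed. The Précis says the results are meant to inform patients' choice of exercise program, so this matters even though the primary comparison does not depend on it.

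**Working it through.** **1. Status, place by place**

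| Analysis | Sections 1.2, 9.1, 9.2 | Section 9.3.1 | Sections 9.3.2–9.3.3 |
|---|---|---|---|
| Aim 2 | exploratory | main | exploratory heading, decided by formal tests |
| Aim 3(a) | exploratory (1.2) | main | main heading, hypothesis-test contrasts |
| Aim 3(b) | exploratory (1.2) | main | exploratory heading, hypothesis-test contrasts |
| Additional mobility measures | not among the main outcomes (9.1) | not mentioned | same Aim 1 series, formal tests |

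Only Aim 3(a) conflicts with 1.2 through a section heading. For Aims 2 and 3(b) the conflict is with one sentence in 9.3.1 and, for Aim 2, with the formal-test sentence in 9.3.3.

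**2. The plan's own figure.** 0.05/4 = 0.0125 reproduces. The divisor 4 does not cover the additional mobility measures fitted in the same series.

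**3. How many tests?** The plan does not say. These counts are assumptions built from its lists.
- Additional mobility measures: 5 if one score per instrument (Gait Efficacy Scale, figure-of-8, challenging gait tasks, gait variability, SPPB). 10 if every listed score is tested: 1 + 2 (time, steps) + 3 (obstacle, curved, narrow) + 3 (stance time, step length, step width) + 1.
- Aim 3(a): 3 if one test each for adverse events, adherence and satisfaction. 15 if 6 expected event types (7.6) + 1 adherence + 8 satisfaction items (five Likert, three yes/no; 6.2.3).

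**4. Chance of at least one false positive.** With k true null hypotheses tested two-sided at level a:
- independent tests: 1 − (1 − a)^k;
- equally correlated z-tests with correlation r: 1 − ∫ [Φ((z − √r·c)/√(1−r)) − Φ((−z − √r·c)/√(1−r))]^k φ(c) dc, where z is the two-sided critical value for a.

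Worked example: k = 10, a = 0.05, r = 0 gives 1 − 0.95^10 = 0.401.

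| Tests | Level | r = 0 | 0.3 | 0.5 | 0.7 |
|---|---|---|---|---|---|
| 5 mobility | 0.05 | 22.6% | 20.9% | 18.3% | 14.8% |
| 10 mobility | 0.05 | 40.1% | 35.1% | 28.7% | 21.3% |
| 5 mobility | 0.0125 | 6.1% | 5.8% | 5.2% | 4.3% |
| 10 mobility | 0.0125 | 11.8% | 10.6% | 8.9% | 6.6% |
| 3 Aim 3(a) | 0.05 (inferred) | 14.3% | 13.6% | 12.5% | 10.9% |
| 15 Aim 3(a) | 0.05 (inferred) | 53.7% | 45.7% | 36.1% | 25.7% |

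**5. Which level applies?** For the mobility measures, the 0.05 rows apply when a real primary effect has made the Hotelling test significant. The 0.0125 rows apply when it has not. If nothing at all differs between the arms, the gate nominally passes only 5% of the time, so 0.0125 is the usual case. For Aim 3(a) no level is stated, and 0.05 is inferred from section 9.2.

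**6. Rare events.** The z-approximation overstates the risk for rare outcomes. Section 7.1 expects cardiac events and falls in under 1% of people. At 1% in both arms with 140 per arm, Fisher's exact test (ignoring clustering) rejects about 0.15% of the time, not 5%.

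**The case against.** A fair reader could say that the plan already draws the needed lines. Sections 1.1 and 1.2 separate primary from secondary objectives. Section 9.1 names LLFDI, 6MWT and gait speed as the main outcomes, and 6.2.1 sets the other gait measures apart as additional. Aim 2 is called exploratory in several places, and 9.3.3 carries 3(b) under the same label. On this view the 9.3.1 sentence is an unrevised line, since Version 1 has the same one. Most of this stands: a reader might infer that nothing distinguishes primary from secondary outcomes, and that would be wrong. It does not settle Aim 3(a), which is main by heading, or the formal-test sentence for Aim 2.

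A second objection is that the two-step rule exists, so it is too strong to infer that everything is tested at full alpha. That is correct for the Aim 1 series, where the level is conditional. Whether the rule was meant to reach Aim 3 is unclear: 9.3.1 mentions it just after Aims 1–3, but 9.3.2 states it under Aim 1 only.

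Third, the counts are uncertain. The Aim 3(a) model takes dichotomous outcomes, five satisfaction items are Likert, and no item-by-item testing is described. This stands, and is why the sizes are given as ranges. Finally, section 1.2 expects similar adverse-event rates, so a chance significant difference there would contradict the stated hypothesis rather than confirm it. It would still be a false safety signal.

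**Conclusion.** The point holds as an inconsistency in status together with a gap in the multiplicity rule. Section 9.3.1 disagrees with 1.2, 9.1, 9.2 and 9.3.3; Aim 3(a) is exploratory in 1.2 and main in 9.3.2; Aim 2 is exploratory yet formally tested. The experimentwise claim in 9.3.1 is not delivered for the additional mobility measures, and nothing is stated for Aims 2 or 3.

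The size is illustrative and rests on assumed counts and equal correlations of 0 to 0.7: about 15–40% for the mobility measures after a gate passed through a real primary effect, about 4–12% if the gate fails, and about 11–54% for Aim 3(a) at an inferred 0.05, lower with rare events. A reader might infer that a false significant secondary result is likely. The documents do not support that: in these scenarios the chance passes one half only with 15 Aim 3(a) tests and near-zero correlation. What can be said is that it is generally well above 5% when tests run at 0.05. The Aim 1 conclusion on the primary outcomes is not affected.

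**What to change.** - In 9.3.1, limit the main analyses and the statement on experimentwise error control to the Aim 1 primary outcomes.
- Move Aim 3(a) out of the main-analysis section so that it agrees with 1.2.
- In 9.3.3, replace the sentence that makes significance the formal test for Aim 2 with a commitment to estimates and intervals.
- State once that Aims 2 and 3 and the additional mobility measures are secondary or exploratory, reported as estimates with 95% confidence intervals and nominal p-values that support no confirmatory claim.

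The cost is wording only: no change to data collection, sample size or models. The downside is that satisfaction, attendance, adverse-event, staff-delivery and additional mobility results can no longer be described as confirmed. If the sponsor wants to confirm any of them, the alternative is to name those outcomes now and bring them under one stated multiplicity procedure.
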